### Recruitment of kindergartens and participants

3.3

This research is conducted in cooperation with the Maternal and Child Health (MCH) Hospital of Jianghan and Hanyang Districts in Wuhan. A sensitization meeting was convened at the MCH Hospital to engage headmasters and doctors from selected kindergartens, where we delivered a comprehensive overview of the project objectives and discussed the planned intervention. It was critical to ensure that headmasters were thoroughly briefed on the study's purpose, and the study design was carefully crafted to align with school schedules and operations, thereby ensuring the feasibility of intervention implementation.

A total of 26 kindergartens (clusters) were selected from Jianghan and Hanyang Districts based on predefined eligibility criteria, including the willingness of the headmasters to participate, the availability of at least two junior classes, low student turnover rates, and no prior participation in similar studies.

Given the structure of the Chinese kindergarten system (which is organized into three grades: junior, middle, and senior), our intervention will enroll children in the middle grade. Within each participating kindergarten, one middle-grade class will be randomly selected, with informed consent obtained from the children's guardians before recruiting them into the project. Child participants must meet the following criteria: enrolled in the middle grade (ages 3–6 years) of participating kindergartens, provide guardian consent, reside in the study district for the full 24-month period, and have no major metabolic/cardiovascular conditions. Exclusion criteria include chronic illnesses requiring specialized care, concurrent participation in other obesity programs, or inability to complete follow-up assessments. The intervention is designed to span 18 months, commencing during the children's second year of kindergarten, and will be seamlessly integrated into daily routines in the intervention group. Following the intervention phase, there will be an additional six-month observational follow-up period.

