## Data collection

5

Table 2 provides an assessment of metrics, methodologies, and data collection schedules used in the study. Trained research personnel will follow standardized protocols and utilize validated tools to ensure data accuracy and consistency across all time points. Assessments were conducted at three key intervals: T1 (baseline) in the second semester of the junior year; T2 (post-intervention) in the second semester of the mid-year; and T3 (follow-up) in the second semester of the senior year.

**Table 2 T2:** Overview of measurement indicators, instruments, and time point of assessment.

Data collection	Indicators	Assessment instruments	Time points of assessment
Measurement in kindergartens	• Height and weight	• Kangwa WS-RT-2U	• T1,T2,T3
	• Waist and hip circumference	• Measuring tape	• T1,T2,T3
	• Body fat percentage	• Multifrequency bioelectric impedance body composition analyzer Inbody 230	• T1,T2,T3
	• Skinfold thickness^a^	• Harpenden Skinfold calipers	• T1,T2,T3
	• Self-regulation level	• Self-regulation related tests	• T1, T2, T3
Actigraph GT3X+	• Physical activity and sleep^a^	• Actigraph GT3X+	• T1, T3
Questionnaire	• Basic information		• T1
	• Dietary behavior	• CEBQ (46), FFQ (48)	• T1,T2,T3
	• Sleep quality in children	• CSHQ (50)	• T1,T2,T3
	• General self-regulation level	• CBQ (51)	• T1,T2,T3
	• Food-related self-regulation level	• CEBQ (46)	• T1,T2,T3
	• Psychological behavior of children	• CBQ (51)	• T1,T2,T3

T1, the second semester of the junior year; T2, the second semester of the middle year; T3, the second semester of the senior year; CEBQ, Children's Eating Behavior Questionnaire; FFQ, food frequency questionnaire; CSHQ, Children's Sleep Habit Questionnaire; CBQ, Children's Behavior Questionnaire.

^a^
These indicators will be measured for some children but not all.

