## Statistical analysis plan

7

The statistical analyses will adhere to the intention-to-treat principle. Participants’ characteristics will be described by study arm. Continuous variables will be presented as mean (standard deviation) or median (interquartile range), depending on distribution, and compared between groups using Student's t-tests for normally distributed data or the Wilcoxon rank-sum test for non-normal variables. Categorical variables will be reported as frequency (%) and compared using the Chi-square test. To address missing data, multiple imputation by chained equations will be used to impute covariates.

The primary analysis will evaluate the impact of the intervention on the primary outcome (e.g., changes in BMI z-score) using a linear mixed-effects regression model. Because BMI z-scores are measured repeatedly for each child at multiple time points (T1-T3), the data have a hierarchical structure, with repeated measures nested within children and children nested within kindergartens. Linear mixed-effects models are therefore employed to account for within-subject correlations over time and clustering by kindergarten, by including random intercepts for both children and kindergartens. For dichotomous outcomes, logistic mixed-effects models will be employed. These models will incorporate a study group (intervention vs. control), and relevant covariates (kindergarten level, child age and sex, and maternal sociodemographic characteristics). The models will also account for the clustered design, and random intercepts for kindergarten and children will be included. Furthermore, the potential mediating role of self-regulation on the association between the intervention and weight status will be explored.

Stratified analysis will examine whether the intervention effect varies across different subgroups. Potential effect modifiers include kindergarten level, child gender, and child age.

All hypothesis tests will use a two-sided *α* = 0.05.

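### Random intercepts alone impose equal correlation across 12- and 24-month gaps, so a visit-specific effect at T3 would get too narrow an interval if correlation falls with time

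*Protocol article*

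**What the plan says.** Section 7 (Statistical analysis plan) describes the primary analysis as a model for "the primary outcome (e.g., changes in BMI z-score) using a linear mixed-effects regression model". It notes that "BMI z-scores are measured repeatedly for each child at multiple time points (T1-T3") and says the models deal with the correlation within a child and within a kindergarten "by including random intercepts for both children and kindergartens". Later in the same paragraph it repeats that "random intercepts for kindergarten and children will be included". It mentions no random slope, residual correlation structure, unstructured covariance or robust variance. The listed fixed effects are study group and covariates. There is no visit term and no group-by-visit term, and no visit is named as primary.

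The footnote to Table 2 in Section 5 (Data collection) fixes the spacing: "T1, the second semester of the junior year; T2, the second semester of the middle year; T3, the second semester of the senior year". Adjacent visits are therefore one school year apart and T1 to T3 is two. Section 3.3 agrees, requiring children to "reside in the study district for the full 24-month period". The Introduction says the three assessments serve to judge both the immediate and the long-term effect of the programme.

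**The concern.** A child random intercept gives every visit the same variance and every pair of visits the same correlation. The model then estimates one within-child residual variance, averaged over the three pairs, and uses it for every contrast between visits. In growing preschool children, measurements two years apart are likely to correlate less than measurements one year apart. If so, the pooled variance is too small for the T1-to-T3 change and too large for T1-to-T2. A large sample does not cure this, because the wrong variance is estimated precisely.

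The overstated precision would fall on T3, the visit that carries the claim of sustained benefit, while T2 would lose power. Section 7 commits every test to a two-sided 5% level.

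**Working it through.** **Inputs from the documents.** Three visits with the spacing above; random intercepts for child and kindergarten; 26 kindergartens, 13 per arm, of about 45 children; 20% attrition; ICC 0.01; two-sided 5% level. The plan gives no figure on this point to reproduce.

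**Assumed inputs.** The documents give no correlation between visits. Four illustrative sets (ρ12, ρ23, ρ13) are used, with equal variances: A (.85, .85, .82), B (.85, .85, .75), C (.90, .90, .81), D (.80, .80, .64).

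**Formulas (balanced data, levels modelled with categorical visit and group-by-visit terms).** Let ρ̄ be the mean of the three correlations. The model's residual variance is proportional to 1 − ρ̄. R is true variance divided by model variance:

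- T3 against T1: R = (1 − ρ13)/(1 − ρ̄)
- T2 against T1: R = (1 − ρ12)/(1 − ρ̄)
- Mean of T2 and T3 against T1: R = (1.5 + 0.5ρ23 − ρ12 − ρ13)/[1.5(1 − ρ̄)]

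If change scores at T2 and T3 are modelled instead, the random-intercept model pools their two variances, so for T3: R = 2(1 − ρ13)/[(1 − ρ12) + (1 − ρ13)].

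In each case type I error = 2[1 − Φ(1.96/√R)], and model SE over true SE is 1/√R.

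**Example, set B.** ρ̄ = (.85 + .85 + .75)/3 = 0.8167. For T3, R = 0.25/0.1833 = 1.364, the SE ratio is 0.86 and the type I error 9.3%.

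| Set | ρ̄ | R at T3 | SE ratio at T3 | T3, levels | T3, change scores | Mean of T2 and T3 vs T1 | T2, levels |
|---|---|---|---|---|---|---|---|
| A | 0.840 | 1.125 | 0.94 | 6.5% | 6.1% | 5.7% | 4.3% |
| B | 0.817 | 1.364 | 0.86 | 9.3% | 8.0% | 7.1% | 3.0% |
| C | 0.870 | 1.462 | 0.83 | 10.5% | 8.7% | 7.7% | 2.5% |
| D | 0.747 | 1.421 | 0.84 | 10.0% | 8.4% | 7.5% | 2.7% |

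With equal correlations every R is 1 and every error is 5.0%.

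**Checks.**

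- Simulation of sets B, C and D (26 kindergartens of 36 children, 6,000 runs each, no true effect) gave 9.4%, 10.2% and 9.9% at T3 on levels. When the T3 change was given its own variance, the error was 5.0–5.5%.
- One mixed model with both random intercepts, fitted to data generated under set B with 45 children per kindergarten, gave an SE of 0.0351 for the T1-to-T3 effect, against 0.0402 from the observed changes. Linear time with group-by-time gave the same 0.0351, so the result does not depend on coding visit as categorical.
- A group main effect averaged over the T2 and T3 change scores, simulated under all four sets, stayed at roughly 4–5%. In balanced data that test compares child means, whose variance the random-intercept model estimates correctly.

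**Kindergarten level.** When levels are modelled, a kindergarten intercept that is constant over visits cancels from any change contrast. It therefore offers no protection if kindergartens differ in how their children change. This is not in the table and would narrow the intervals further.

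**The case against.** The strongest reply is that the inflated contrast is not in the model as listed. Section 7 names a group effect and covariates, with no group-by-visit term and no primary visit. If the outcome is the change score and only an averaged group effect is tested, the type I error is about nominal. This stands, and it limits the point. A reader might infer that the primary test is wrong as written; the document does not support that, because it does not say which contrast is tested. But an averaged effect cannot separate immediate from long-term impact, which the Introduction sets as the purpose of the three visits. Once T3 is tested on its own, the problem arises.

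A second reply is that every correlation is assumed. That also stands. A reader might infer that the T1-to-T3 correlation is known to be lower, or that T3 false positives are established at some particular rate. Neither follows. A fall from .85 to .82 gives 6.5% on levels, and a smaller fall approaches 5%. Child-specific growth slopes, which also make the variances unequal, could exceed the tabulated range: one assumed scenario gave 13.2%.

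A third reply is that covariance structure belongs in a full analysis plan, which is not shown and could add a residual structure. That is possible. But the article does not leave the matter open: it names random intercepts as the device for within-child correlation and says so twice. The point concerns that stated choice, not a missing detail.

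**Conclusion.** The point holds conditionally. It requires that the effect be estimated at T3 relative to T1, or as the mean of T2 and T3 against T1 on levels, and that correlation fall with the time gap. Under the four assumed sets, the T3 interval on levels is 6–17% too narrow and the type I error about 6.5–10.5%. The T3 error is 6.1–8.7% if change scores are modelled, and the averaged baseline contrast on levels gives 5.7–7.7%. The T2 test on levels is conservative, at 2.5–4.3%. These figures illustrate a range and are not estimates for this trial. Since the long-term claim needs a T3 contrast and the remedy is cheap, the change should be made.

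**What to change.** In Section 7:

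1. Model visit as categorical with group-by-visit terms, and name the primary visit contrast.
2. Replace the child random intercept with an unstructured 3×3 within-child covariance.
3. Let the kindergarten effect vary by visit through a kindergarten-by-visit random effect, instead of relying on a constant intercept alone.
4. Use small-sample degrees of freedom (Kenward–Roger or Satterthwaite), because there are only 26 clusters.

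No new data are needed. The within-child covariance has six parameters instead of two, and the kindergarten part gains at least one. The within-child parameters are readily estimated from about 1,000 children (26 × 45 = 1,170 enrolled, 936 after 20% attrition). The kindergarten-by-visit variance rests on the 26 clusters, which is why item 4 is needed. T3 intervals on levels become wider, by 6–21% under the four assumed sets (√R from 1.06 to 1.21). That is the correction itself, not lost efficiency. If the correlations are in fact equal, the revised model remains valid and costs almost nothing.

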**Methods:**

This stratified randomized controlled trial enrolls children from 26 Wuhan kindergartens (13 intervention, 13 control) over 18 months. The multicomponent intervention targets diet, physical activity, sleep, sedentary behavior, and self-regulation, engaging children, families, and kindergarten environments. Control groups follow standard curricula. Primary outcome is the change in BMI z-score. Secondary outcomes assess behavioral factors (diet, sleep, activity), self-regulation skills, and other anthropometric indicators. Analyses adhere to intention-to-treat principles, using linear mixed models to evaluate intervention effects across strata while exploring potential effect modifiers including kindergarten level, child gender, and age.

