### Sample size determination

3.2

The unit is randomization is the kindergarten. We calculated the sample size in Power Analysis and Sample Size (PASS) using a test for two means in a cluster-randomized design. Assuming each kindergartens contribute approximately 45 children, we determined that 11 kindergartens per arm (intervention and control) would provide 90% power (1-*β*) to detect an underlying difference of 0.28 (60) in the mean outcome (a medium standardized effect size) following the intervention. This calculation assumes an intra-class correlation coefficient (ICC) of 0.01 (61) at the two-sided significance level (*α*) of 5%. Assuming up to 20% attrition, we increased the sample to 26 kindergartens (13 intervention) (45 children/kindergarten), yielding an anticipated sample of 585 preschoolers receiving intervention.

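### Stratified analysis is the only method named for examining effect modification, and on its own it does not test whether the effect differs between subgroups

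*Protocol article*

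**What the plan says.** Section 7 (Statistical analysis plan) gives subgroups two sentences: "Stratified analysis will examine whether the intervention effect varies across different subgroups" and "Potential effect modifiers include kindergarten level, child gender, and child age". The model description just before them lists main effects only: "These models will incorporate a study group (intervention vs. control), and relevant covariates", the covariates being kindergarten level, child age and sex, and maternal sociodemographic characteristics, with random intercepts for kindergarten and child. No product of study group with a modifier is listed, and no interaction or heterogeneity test appears elsewhere in the article. The Abstract (Methods) takes the same line: "using linear mixed models to evaluate intervention effects across strata while exploring potential effect modifiers". Section 7 closes with a general rule, "All hypothesis tests will use a two-sided" level of 0.05, and gives no separate rule for subgroups.

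**The concern.** Whether an effect varies is a question about the difference between subgroup effects. A stratified analysis gives one estimate and one p value per stratum. Without a further step, a reader tends to compare significance: an effect in girls at p<0.05 and none in boys is taken as a difference. Each stratum has less power than the whole trial, so this pattern arises readily when the effect is identical in both.

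Kindergarten level raises a second problem. It is a property of the cluster, so stratifying by it divides the 26 kindergartens themselves, and each stratum must estimate its own between-kindergarten variance from fewer clusters.

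At stake is a subgroup claim drawn from noise. Section 8 expects the findings to inform programme design and policy, so such a claim could be taken up. The overall test of the intervention is not affected.

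**Working it through.** **Inputs.** From section 3.2: difference 0.28, ICC (ρ) 0.01, about 45 children per kindergarten, 11 kindergartens per arm raised to 13, attrition up to 20%, so m = 45 × 0.8 = 36 at the low end. Two-sided α is 0.05. Assumed: SD = 1 (the article calls 0.28 a standardized effect but gives no SD), a simple two-arm comparison of means with known variance, and two equal subgroups per modifier.

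**The plan's own figure.** Section 3.2 states that 11 kindergartens per arm "would provide 90% power" "to detect an underlying difference of 0.28". With SE = √{2[ρ + (1−ρ)/m]/K}:

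- m = 45, K = 11: SE = 0.0763, power 95.6% (normal) or 93.7% (t with 20 df).
- m = 36, K = 11: SE = 0.0826, power 92.4% (normal) or 89.7% (t).

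The stated inputs with SD = 1 therefore give more than 90%; 36 analysed children per cluster with the t test match it. The point below does not depend on this. The article gives no figure for the subgroup analyses.

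**Subgroup standard errors, K = 13 per arm.**

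- Gender or age (both subgroups lie inside each kindergarten, m/2 children each): variance = 2[ρ + (1−ρ)/(m/2)]/13. For m = 45, 2(0.01 + 0.99/22.5)/13 = 0.00831, SE 0.0911. For m = 36, 2(0.01 + 0.99/18)/13 = 0.0100, SE 0.1000. The two estimates share clusters, with covariance 2ρ/13 = 0.00154, a correlation of 0.19 or 0.15.
- Kindergarten level (two levels, 6.5 kindergartens per arm on average): variance = 2[ρ + (1−ρ)/m]/6.5. For m = 45, SE 0.0992; for m = 36, SE 0.1074. The two estimates are independent.

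**Chance that exactly one of two subgroups has p<0.05 when the true effect is the same in both** (200,000 simulated trials per row; direct calculation from the standard errors above agrees to within 0.3 percentage points):

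| True effect | Gender or age, m = 45 | Gender or age, m = 36 | Kindergarten level, m = 45 | Kindergarten level, m = 36 |
|---|---|---|---|---|
| 0 | 9.2% | 9.4% | 9.5% | 9.5% |
| 0.14 | 39.6% | 37.3% | 41.3% | 37.9% |
| 0.20 | 42.6% | 45.0% | 50.0% | 49.5% |
| 0.28 | 21.3% | 29.6% | 31.2% | 38.2% |

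One cell by hand: kindergarten level, m = 45, effect 0.28. The ratio is 0.28/0.0992 = 2.82, power per stratum 0.807, and 2 × 0.807 × 0.193 = 0.31.

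**Three modifiers at 0.28, treated as independent.** At least one discordant pair: 1 − (1 − 0.213)² × (1 − 0.312) = 57% for m = 45, and 1 − (1 − 0.296)² × (1 − 0.382) = 69% for m = 36.

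**Interaction test, same simulated trials.** It rejects in 5% for each modifier at every effect size. Over three modifiers, 1 − 0.95³ = 14% if independent.

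**Clusters per stratum.** The article does not give the number of kindergarten levels. Two levels leave 13/2, about 6 or 7 per arm per stratum; three leave 13/3, about 4.

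**The case against.** The strongest reply is that the article neither rules out an interaction test nor says that p values will be compared across strata. It is a condensed account, and stratified estimates can be accompanied by a heterogeneity test set out in a fuller plan. That is correct as far as it goes. A reader might infer that interaction tests are excluded, or that each stratum will be judged at 0.05 and the verdicts compared; the text supports neither. The 0.05 rule is a general statement. The point stands in a narrower form: the article does not leave the method open. It poses the question and names a method which, alone, does not answer it.

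A reader might also halve a trial with exactly 90% power: 3.24/√2 = 2.29, power 63% per half, and 2 × 0.63 × 0.37 = 47% discordance. That holds only for independent halves at exactly that power. Gender and age subgroups share kindergartens, and on the stated inputs 13 per arm gives more than 90%, so at 0.28 the figures are 21-30% for gender or age and 31-38% for kindergarten level.

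Nor can it be said that the kindergarten variance becomes impossible to estimate. The number of levels is not given, so only a loss of stability is supported.

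Finally, the Abstract speaks of exploring the modifiers, and section 7 calls them potential. This lowers the severity; it does not make the method fit the question.

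**Conclusion.** The point holds in this form: stratified analysis is the only method named for effect modification by kindergarten level, gender and age, and it does not by itself test effect modification. If strata are judged by which reaches p<0.05, a false contrast between two subgroups appears in about 21-50% of trials when a common effect of 0.14-0.28 exists, and in about 9-10% when there is none, against 5% for an interaction test. These figures rest on an SD of 1, ICC 0.01, 13 kindergartens per arm with 36-45 children, two equal subgroups, and a way of reading the strata that the article does not state. The weaker kindergarten variance under stratification by level is a secondary point whose size depends on the unstated number of levels. Severity is minor to moderate: the analyses are exploratory and the primary conclusion is unaffected.

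**What to change.** Replace the sentence on stratified analysis with wording such as: *Effect modification by kindergarten level, child gender and child age will each be tested by adding the modifier (if not already included) and its interaction with treatment to the primary mixed model fitted to all children. The interaction will act on the term that carries the intervention effect in that model. The interaction estimate will be reported with its 95% CI and p value. Subgroup estimates will be taken from the same model and labelled exploratory.*

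Tying the interaction to whichever term carries the intervention effect avoids presuming a group-by-visit model, which section 7 does not list. Fitting one model to all children also keeps all 26 kindergartens in the estimate of the kindergarten variance.

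The cost is slightly more analysis work and no new data. The interactions will have low power, and the report should say so. The SE of the difference between two subgroup effects is √(2 × variance − 2 × covariance): 0.116 to 0.130 for gender or age and 0.140 to 0.152 for a two-level kindergarten split. At 80% power (2.80 × SE) the smallest detectable differences are about 0.33-0.36 and 0.39-0.43, larger than the overall effect of 0.28. A non-significant interaction should therefore not be read as evidence of a uniform effect.
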